## Abstract

**Background:**

Inflammation plays a key role in the pathophysiology of coronary heart disease (CHD) and its acute manifestation, acute coronary syndrome (ACS). Aging is associated with a decline of the immune system, a process known as immunosenescence. This is characterized by an increase in highly proinflammatory T cells that are involved in CHD progression, plaque destabilization, and myocardial ischemia–reperfusion injury. Telomere dysfunction has been implicated in immunosenescence of T lymphocytes. Telomerase is the enzyme responsible for maintaining telomeres during cell divisions. It has a protective effect on cells under oxidative stress and helps regulate flow-mediated dilation in microvasculature.

**Objective:**

The TACTIC (Telomerase ACTivator to reverse Immunosenescence in Acute Coronary Syndrome) trial will investigate whether a telomerase activator, TA-65MD, can reduce the proportion of senescent T cells in patients with ACS with confirmed CHD. It will also assess the effect of TA-65MD on decreasing telomere shortening, reducing oxidative stress, and improving endothelial function.

**Methods:**

The study was designed as a single-center, randomized, double-blind, parallel-group, placebo-controlled phase II trial. Recruitment started in January 2019. A total of 90 patients, aged 65 years or older, with treated ACS who have had CHD confirmed by angiography will be enrolled. They will be randomized to one of two groups: TA-65MD oral therapy (8 mg twice daily) or placebo taken for 12 months. The primary outcome is the effect on immunosenescence determined by a decrease in the proportion of CD8+ TEMRA (T effector memory cells re-expressing CD45RA [CD45 expressing exon A]) cells at 12 months. Secondary outcomes include leukocyte telomere length, endothelial function, cardiac function as measured by echocardiography and NT-proBNP (N-terminal fragment of the prohormone brain-type natriuretic peptide), systemic inflammation, oxidative stress, and telomerase activity.

**Results:**

The study received National Health Service (NHS) ethics approval on August 9, 2018; Medicines and Healthcare products Regulatory Agency approval on October 19, 2018; and NHS Health Research Authority approval on October 22, 2018. The trial began recruiting participants in January 2019 and completed recruitment in March 2020; the trial is due to report results in 2021.

**Conclusions:**

This pilot trial in older patients with CHD will explore outcomes not previously investigated outside in vitro or preclinical models. The robust design ensures that bias has been minimized. Should the results indicate reduced frequency of immunosenescent CD8+ T cells as well as improvements in telomere length and endothelial function, we will plan a larger, multicenter trial in patients to determine if TA-65MD is beneficial in the treatment of CHD in elderly patients.

**Trial Registration:**

ISRCTN Registry ISRCTN16613292; http://www.isrctn.com/ISRCTN16613292 and European Union Drug Regulating Authorities Clinical Trials Database (EudraCT), European Union Clinical Trials Register 2017-002876-26; https://tinyurl.com/y4m2so8g

**International Registered Report Identifier (IRRID):**

DERR1-10.2196/19456

## Introduction

### Background

Inflammation plays a key part in the pathophysiology of coronary heart disease (CHD) and its acute manifestation—acute coronary syndrome (ACS)—from atheroma formation to plaque rupture [1]. Despite contemporary treatment, recurrent adverse events (AEs) post-ACS remain common, especially in the elderly [2]. Aging is associated with a decline of the immune system, a process known as immunosenescence [3], leading to an increased burden of disease. Targeting interleukin 1 (IL-1β), the principal cytokine of innate immunity, in patients with previous myocardial infarction (MI) has been shown to reduce subsequent adverse cardiovascular outcomes [4]. Furthermore, the contribution of the adaptive immune system to the complex inflammatory response evoked during ACS has been demonstrated extensively in experimental and clinical studies [5]. In particular, highly proinflammatory senescent T cells are thought to be key players in plaque destabilization [6] and myocardial ischemia–reperfusion injury [7].

Telomere dysfunction has been implicated in immunosenescence of T cells [3,8]. Telomeres are DNA caps that protect the ends of chromosomal DNA. They are widely regarded as the internal biological clock of a living organism and shorten by a few base pairs with every cell division. This process can be slowed down by activation of telomerase, which is responsible for producing and maintaining telomeres. Shorter lymphocyte telomeres are associated with development of CHD as well as increased cardiovascular risk and mortality independent of conventional vascular risk factors [9-12]. Alleles associated with shorter telomere length (TL) were also associated with an increased risk of CHD, suggesting a causal relationship [13].

The TACTIC (Telomerase ACTivator to reverse Immunosenescence in Acute Coronary Syndrome) trial was designed to test whether a telomerase activator can reduce the proportion of senescent T cells in patients following ACS. There is accumulating evidence that telomerase, through its telomerase reverse transcriptase (TERT) catalytic subunit, contributes to cell physiology independently of its ability to elongate telomeres. We and our collaborators have demonstrated the effect of oxidative stress on telomerase as well as a telomere-independent protective effect of telomerase in cells under oxidative stress [14,15]. Telomerase activity (TA) has also been shown to regulate endothelial flow-mediated dilation (FMD) [16].

The small molecule cycloastragenol (CAG), isolated from the roots of the herb astragalus, is the only available telomerase activator in humans. TA-65MD is a purified and encapsulated form of CAG with increased bioavailability (T.A. Sciences). We have also shown that TA-65MD induces telomerase and proliferation in CD4 T lymphocytes in a TERT-dependent way [17]. In a randomized controlled trial investigating cytomegalovirus (CMV)-positive healthy subjects aged 53-87 years old, subjects taking 8 mg of TA-65MD daily increased TL over the 12-month period, whereas subjects in the placebo group significantly lost TL [18].

### Trial Rationale

The evidence indicates that telomerase deficiency in atherosclerosis leads to accelerated immunosenescence with telomere shortening in peripheral blood leukocytes, increased oxidative stress and inflammation, and impaired microvascular endothelial function, all of which contribute to CHD progression. We hypothesize that activating telomerase with TA-65MD will lead to reduced immunosenescence, decreased telomere shortening, and improved endothelial function in patients with CHD. The null hypothesis is that there will be no difference in immunosenescence between the two groups following 12 months of treatment with TA-65MD or placebo. The choice of active treatment versus placebo is appropriate in this population where no telomerase activator is currently used as part of usual care. All patients will receive usual care alongside the trial.

### Objectives

#### Primary Objective

We aim to assess the effect of 8 mg of oral TA-65MD given twice daily for 12 months on immunosenescence in older patients following ACS.

#### Secondary Objectives

The secondary objectives of this trial are as follows:

To investigate the effect of 1-year TA-65MD treatment on leukocyte TL.To investigate the effect of 1-year TA-65MD treatment on microvascular endothelial function.To investigate the effect of 1-year TA-65MD treatment on systemic inflammation and heart failure, reflected by expression of N-terminal fragment of the prohormone brain-type natriuretic peptide (NT-proBNP) and high‐sensitivity C‐reactive protein (hsCRP).To investigate the effect of 1-year TA-65MD treatment on measures of cardiac function as measured by echocardiography.To investigate the effect of TA-65MD treatment on TA and oxidative stress.To investigate the effect of TA-65MD treatment on clinical events—all-cause death, stroke, or MI—in patients after 1 year.To characterize the AE profile of TA-65MD.To quantify adherence to study drugs.To investigate the impact of seropositivity to CMV at baseline on trial outcomes.

## Methods

### Trial Design

This is a single-center, randomized, double-blind, parallel-group, placebo-controlled phase II trial comparing TA-65MD with placebo in 90 participants with CHD who have had ACS in the 6 months prior to consent. A total of 90 patients will be randomized to either the TA-65MD group (n=45) or the placebo group (n=45); TA-65MD and placebo will be taken by these groups, respectively, twice daily for 12 months. The schedule of this trial is shown in Table 1. The trial will run according the International Conference on Harmonisation (ICH)-Good Clinical Practice (GCP) and in accordance with relevant UK legislation and the trial protocol. This trial was registered at the International Standard Randomized Controlled Trial Number (ISRCTN) registry (16613292) and at the European Union Drug Regulating Authorities Clinical Trials Database (EudraCT), European Union Clinical Trials Register (2017-002876-26).

**Table 1 table1:** Trial schedule of assessments and interventions.

Schedule items		Time of assessments and interventions						
		Baseline^a^	Day 1	1 month (wks 3-5)	3 months (wks 11-15)	6 months (wks 24-28)	9 months (wks 37-41)	12 months (wks 50-54)
**Enrollment**								
	Eligibility screen	X						
	Informed consent	X						
**Assessments**								
	Blood pressure	X		X	X	X	X	X
	Capillary glucose	X		X	X	X	X	X
	Physical assessment of height and weight	X						
	Venous sample (5 mL) cytomegalovirus IgG^b^	X						
	Venous sample (4 mL) CD8 TEMRA^c^ immunosenescence (primary outcome)^d^	X				X		X
	Venous sample (36 mL) CD8 and CD4 immunosenescence (secondary outcomes), telomere length, and telomerase activity	X				X		X
	Venous sample (4 mL) oxidative stress, future use	X				X		X
	Venous sample (5 mL) future research use—optional consent	X				X		X
	Venous sample (5mL) hsCRP^e^ and NT-proBNP^f^	X				X		X
	Endothelial function (EndoPAT [Peripheral Arterial Tone])	X				X		X
	Echocardiography	X						X
**Interventions**								
	Randomization—stratified	X						
	Dispensing of investigational medicinal product (IMP)		X	X	X	X	X	X
	Return of unused IMP and drug adherence			X	X	X	X	X
	Adverse events evaluation			X	X	X	X	X

^a^Baseline assessments are completed after written consent is obtained and are performed before randomization.

^b^IgG: immunoglobulin G.

^c^TEMRA: T effector memory cells re-expressing CD45RA (CD45 expressing exon A).

^d^Results from baseline immunosenescence sample are required for randomization.

^e^hsCRP: high‐sensitivity C‐reactive protein.

^f^NT-proBNP: N-terminal fragment of the prohormone brain-type natriuretic peptide.

### Primary Outcome

The primary outcome is immunosenescence following 12 months of treatment with TA-65MD. Immunosenescence will be determined by flow cytometry and fluorescence-activated cell sorting (FACS) (see Figure 1); the proportion of terminally differentiated CD8+ effector memory cells (% CD8+ TEMRA [T effector memory cells re-expressing CD45RA (CD45 expressing exon A)]) will be calculated from the total number of peripheral blood CD8+ T lymphocytes. We have previously demonstrated the prognostic utility of CD8+ TEMRA as a measure for immunosenescence [19]. The mean difference between the intervention and control arms will be compared at 12 months.

**Figure 1 figure1:**
[figure not shown]
Example gating path for seven-color fluorescence-activated cell sorting (FACS) from ethylenediaminetetraacetic acid (EDTA) peripheral blood. AF700: Alexa Fluor 700; APC: allophycocyanin; BV421: Brillian Violet 421; CCR7: C-C chemokine receptor type 7; CD45RA: CD45 expressing exon A; CM: central memory; CX3CR1: C-X3-C motif chemokine receptor 1; EM: effector memory; FITC: fluorescein isothiocyanate; FSC: forward scatter; FSC-H: forward scatter-pulse height; PE: phycoerythrin; PE-Cy7: phycoerythrin and cyanine 7; SSC: side scatter; TEMRA: T effector memory cells re-expressing CD45RA; V500: violet 500.

### Secondary Outcomes

#### CD8 T Cell Telomere Length

TL will be determined from cryopreserved peripheral blood mononuclear cells (PBMCs) by flow cytometry-fluorescent in situ hybridization (flow-FISH) [9]. TL will be measured in total leukocytes and CD8+ T cells. CD8+ T cell TL is significantly reduced in patients with CHD and post-MI [9]. We expect TL in CD8+ T cells to decrease less in patients treated with TA-65MD. TL will be measured in total leukocytes and in CD8+ T cells at baseline, 6 months, and 12 months.

#### Microvascular Endothelial Function

Microvascular endothelial function will be assessed by measuring FMD at baseline, 6 months, and 12 months. Using plethysmography at the fingertips of both hands, the EndoPAT (Peripheral Arterial Tone) system (Itamar Medical Ltd) will calculate an index of pulse wave amplitude after cuff occlusion to before occlusion of the test arm divided by the same ratio of the control arm, namely the reactive hyperemic index. FMD has been shown to be compromised in patients with CHD and microvascular dysfunction as a predictor of adverse clinical outcome [20].

#### Systemic Inflammation

Systemic inflammation will be assessed using the hsCRP, which is a downstream biomarker of inflammation associated with an increased risk of cardiovascular events [21].

#### Cardiac Function

Cardiac function will be assessed by NT-proBNP and transthoracic echocardiography at baseline and 12 months. Together, these measures will determine myocardial function, strain (NT-proBNP), and global longitudinal strain, reflecting the pathophysiological targets of heart failure. Lack of telomerase and presence of shortened telomeres in cardiomyocytes from preclinical models (ie, mice) have been shown to be critical in the development of heart failure in that species [22]. Patients with chronic heart failure have shorter TL compared to age- and gender-matched controls with incremental attrition according to the presence and extent of coronary artery disease (CAD) [23].

#### Telomerase Activity

TA will be assessed by a modified telomeric repeat amplification protocol (TRAP) assay, using digital droplet polymerase chain reaction (PCR) [24,25]. This provides an indication of drug effect: TA-65MD is expected to increase TA in PBMCs.

#### Oxidative Stress

Oxidative stress will be measured with the thiobarbituric acid reactive substances (TBARS) colorimetric assay (Oxford Biomedical Research) from freshly collected and cryopreserved plasma. TBARS is an established assay to quantify lipid peroxides [26].

#### Seropositivity to Cytomegalovirus

The effect of CMV seropositivity at baseline will be correlated with study outcomes using an exploratory analysis. CMV is a highly prevalent human herpes virus with CMV seropositivity present in a large proportion of elderly patients. CMV-directed cells increase with age, constituting a large proportion of the total CD8+ T cell pool in elderly individuals [27]. T cell responses to CMV are restricted to a limited number of epitopes, resulting in progressive, prolonged oligoclonal expansion of CMV-specific CD8+ T cells in a process known as memory inflation [28]. We have previously shown that individuals who are seropositive have a much higher proportion of CD8+ TEMRA cells and have a greater risk of heart attacks [7,29].

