#### Randomization

Randomization will be performed using the Sealed Envelope Ltd system with a minimization scheme to ensure patients randomized to each group are comparable at baseline. The minimization scheme will account for (1) gender (male or female), (2) type of ACS (ST elevation myocardial infarction [STEMI] or non-ST elevation myocardial infarction [NSTEMI]), and (3) CD8+ TEMRA (high >45% or low ≤45%) at baseline.

Eligible patients will be randomized by delegated and trained members of the research team at each center using the 24-hour, central, secure, web-based randomization system with concealed allocation. Eligible patients will be randomized in a 1:1 ratio to receive TA-65MD (intervention under study) or placebo (control arm).

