#### Statistical Analysis

Primary analysis will follow intention-to-treat principles with patient data analyzed according to randomization and irrespective of intervention received; other analysis groups, such as per-protocol groups, may be considered subsequently. Every effort will be made to retain and include all patients who are part of the trial.

Data will be summarized by study group. Mean or median will summarize continuous variables, whereas number and percentage will be used to summarize categorical variables. A general linear model will be used to analyze the primary outcome considering all covariates used in the randomization scheme. Similar methods will be used to analyze all continuous secondary outcomes. Data of other types will be analyzed using generalized linear models with appropriate distributions.

The numbers of MACCE after 12 months will be compared between arms by the use of standardized rates (eg, by consideration of the number of events per patient month in each arm). Impact of missing data will be explored by tabulating the proportion of missing data in each arm. A full statistical analysis plan will be developed for the outcome measures and agreed upon with the IDMEC and the chief investigator prior to any analysis being undertaken.

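### CMV serostatus, measured at baseline and described as strongly related to the primary outcome, is not among the stated model covariates, and the planned correlation cannot show whether the drug effect differs by serostatus

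*Protocol article*

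**What the plan says.** All references are to the Protocol article; no SAP is shown.

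- **CMV and the primary outcome.** Under Seropositivity to Cytomegalovirus, the authors report from their earlier work that "individuals who are seropositive have a much higher proportion of CD8+ TEMRA cells". They give no size for the difference. They describe "CMV seropositivity present in a large proportion of elderly patients" but give no prevalence.
- **Measurement.** The schedule in Table 1 lists "Venous sample (5 mL) cytomegalovirus IgG" at baseline.
- **Objective.** The last secondary objective is "To investigate the impact of seropositivity to CMV at baseline on trial outcomes".
- **Stated CMV analysis.** "The effect of CMV seropositivity at baseline will be correlated with study outcomes using an exploratory analysis".
- **Primary model.** Under Statistical Analysis: "A general linear model will be used to analyze the primary outcome considering all covariates used in the randomization scheme". Similar methods apply to the continuous secondary outcomes. Under Randomization, those covariates are gender, ACS type and "CD8+ TEMRA (high >45% or low ≤45%) at baseline". CMV is not one of them.
- **Context.** The Background cites randomized evidence on telomere length from "cytomegalovirus (CMV)-positive healthy subjects aged 53-87 years old". The eligibility criteria of this trial do not mention CMV. The Statistical Considerations overview says the estimates are to inform a large multicenter trial.

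**The concern.** Two separate things are at stake.

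1. **Precision and chance imbalance.** A baseline variable that the authors regard as strongly related to the primary outcome is already collected but is not in the stated covariate set. Baseline TEMRA enters only as a two-level factor, so it can absorb only part of what CMV predicts. The remainder stays in the residual variance, and a chance difference in serostatus between arms goes uncorrected.
2. **The question the CMV analysis answers.** Correlating serostatus with outcome says whether seropositive patients have different TEMRA levels. The authors say they have shown that already. For planning the larger trial, the more useful quantity is the treatment effect within each serogroup, because the cited randomized evidence came from CMV-positive subjects while this trial sets no CMV entry criterion. The stated method does not estimate it.

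**Working it through.** The plan has no figure to reproduce on this point. The 90 patients (45 per arm) come from a pilot-study convention, not a power calculation. CMV prevalence, the CMV difference in TEMRA and the baseline-to-12-month correlation are not given, so the values below are assumptions shown as ranges. SD means the within-serogroup SD of % CD8+ TEMRA.

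**Step 1. Can a correlation detect effect modification?** Assume 70% seropositive, so the variance of serostatus is 0.7 × 0.3 = 0.21, with 1:1 allocation and residual variance 1. Compare two cases with the same average CMV gap of 1.0 SD across arms:

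- *Uniform effect:* drug effect −0.3 SD in both serogroups. Outcome variance = 1 + 0.21 + 0.3² × 0.25 = 1.2325. Correlation = √0.21 / √1.2325 = 0.41.
- *Effect in seropositives only:* 0 versus −0.6 SD, with a CMV gap of 1.3 SD on placebo and 0.7 SD on drug. Outcome variance = 1 + 0.21 + 0.7 × 0.6² × 0.25 = 1.273. Correlation = √0.21 / √1.273 = 0.41.

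Simulation gave 0.412 and 0.406. A correlation across all patients is practically the same in two situations with opposite implications for the next trial.

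The article does not say whether the arms would be pooled. If the correlation were run within each arm, the second case would give 1.3√0.21 / √(1 + 1.3² × 0.21) = 0.51 on placebo and 0.7√0.21 / √(1 + 0.7² × 0.21) = 0.31 on drug. That hints at a difference, but still gives no treatment effect by serogroup and no confidence interval for one.

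**Step 2. What does CMV add to the planned model?** Large-sample simulation: CMV shifts baseline and 12-month TEMRA equally, by 0.5 to 1.5 SD; prevalence is 50% to 85%; the within-serogroup correlation between baseline and 12 months is 0.6 to 0.9; a median split stands in for the 45% cut.

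| Baseline TEMRA in model | Cut in residual variance from adding CMV | CI narrower by 1 − √(1 − cut) |
|---|---|---|
| Split in two | 1.1% to 16.4% | 0.6% to 8.6% |
| Continuous | 0.1% to 8.2% | 0.05% to 4.2% |

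**Step 3. Chance imbalance.** Under simple randomization the SD of the between-arm difference in seropositivity is √(2p(1 − p)/45), which is 10.5, 9.7 and 8.4 percentage points at p = 0.5, 0.7 and 0.8. By the normal approximation, a difference of 10 points or more occurs in 34%, 30% and 24% of trials. Minimizing on TEMRA should lower this somewhat. With a 1 SD CMV difference, prevalence 50% to 80% and the model of step 2, CMV keeps a coefficient of 0.43 to 0.64 SD after the split. A 10-point imbalance therefore moves the adjusted contrast by 0.10 × 0.43 to 0.10 × 0.64, or 0.04 to 0.06 SD. The standard error of that contrast in the same simulation is about 0.16 to 0.20 SD, so the shift is roughly 27% to 33% of one standard error.

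**Step 4. Precision of a treatment-by-CMV estimate.** In residual SD units, SE(main) = √(2/45) = 0.211 and SE(interaction) = √(2/(45p) + 2/(45(1 − p))). Their ratio is 1/√(p(1 − p)):

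| p | Ratio | SE(interaction) | Detectable at 80% power | Power for 0.6 SD |
|---|---|---|---|---|
| 0.5 | 2.00 | 0.42 | 1.18 | 30% |
| 0.7 | 2.18 | 0.46 | 1.29 | 26% |
| 0.8 | 2.50 | 0.53 | 1.48 | 21% |
| 0.9 | 3.33 | 0.70 | 1.97 | 13% |

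(Two-sided 5% level assumed, no dropout.) At p = 0.8 about 45 × 0.2 = 9 seronegative patients per arm remain.

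**The case against.** The strongest reply is that this is detail for the SAP. The article defers to a full SAP agreed before any analysis, and it says the model will consider the randomization covariates, without saying that no others may enter. The CMV objective and the stated CMV analysis also agree with each other: both concern outcomes, and the analysis is labelled exploratory. With 90 patients, an interaction estimate will be imprecise whatever is done.

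Much of this stands. Nothing stated is contradictory, no figure is wrong, and the unseen SAP may already do better. Keeping CMV exploratory is reasonable. But the correlation and the covariate set are written statements of method, and a SAP that followed them would carry the weakness forward.

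Three stronger readings are tempting, and the document does not support them:

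- *The primary comparison is biased without CMV.* It is not. Allocation is randomized, and ordinary chance imbalance is already reflected in the standard error. Baseline TEMRA, itself strongly related to CMV, is both minimized on and in the model.
- *The gain from adjustment is large.* For a 1 SD difference at 70% prevalence, CMV alone would explain 0.21/1.21 = 17% of outcome variance, giving a 9% narrower interval, and a 10-point imbalance would shift an unadjusted contrast by 0.10 SD. Those figures belong to a model with no baseline TEMRA term, which is not the planned one.
- *The trial promises a test of effect modification, or states that it will pool the arms, and so fails its own objective.* The objective speaks only of impact on outcomes, and the article does not say how the arms will be handled in the correlation.

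**Conclusion.** The point holds as a worthwhile improvement to two stated methods, not as an error that undermines the trial. The correlation is the main part: as worded, it estimates a prognostic association and cannot show whether the effect of TA-65MD differs by serostatus. This follows from the form of the analysis; the 70% prevalence in step 1 only illustrates it. The covariate part is secondary. Under the planned model the gain is a confidence interval about 0.6% to 8.6% narrower, plus removal of a shift of about 0.04 to 0.06 SD per 10 points of chance imbalance. If baseline TEMRA were entered as a continuous variable, most of that precision gain would disappear. The precision and imbalance figures rest on the assumed prevalence, CMV difference and correlations, and on a median split standing in for the 45% cut.

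**What to change.** In the SAP, before any analysis and before unblinding:

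1. Add baseline CMV IgG status (positive or negative) as a covariate in the primary model and in the models for the continuous secondary outcomes.
2. Replace the correlation with a model containing a treatment-by-CMV term. Report the treatment effect with its 95% CI in each serogroup and the interaction estimate with its CI. Label this exploratory and for estimation only, with no significance claim.

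**Cost:** SAP wording and one degree of freedom for the covariate. No new data are needed, since the sample is already scheduled at baseline. The downside is an imprecise interaction, and a thin seronegative group if prevalence is high; the report should give the number of patients in each serogroup by arm so that readers can judge this.
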